#### Secondary analyses of primary aims

Our a priori secondary analyses entail examining if there are sub-groups with differences in HIV/AIDS and HIV testing knowledge improvement or retention in the short- and longer-term. We will assess the impact of demographic characteristics, HIV testing history, and testing site for all participants, as well as nativity and US acculturation for Latino participants in these secondary analyses. For these secondary analyses, we will use the aforementioned generalized linear mixed-effect models to take into account the two-arm clinical trial design; language and health literacy level; the repeated measures, the longitudinal data that are collected at baseline and follow-up assessments; and the covariates of interest (e.g., demographic characteristics and HIV testing history). Our focus of analysis will be the main effects of the covariates of interest and their interaction effects with study arm, stratifying factors and time. For longer-term retention of knowledge, we also will examine the impact of repeated testing during the follow-up period.

#### Secondary aims and exploratory aim analyses

Our main secondary aim is assessing HIV re-testing behavior (Table 5). For our sample size (*n = 150/stratum*), we will have adequate power to detect a ≥ 15% absolute difference (Δ) in HIV testing behaviors (re-testing at 12 months, HIV testing outside of the study) by group within strata (information delivery mode, language and health literacy level) (assumes ≥75% follow-up, β = 0.2, α = 0.05). A ≥ 15%Δ is reasonable, per other HIV testing research [16, 66, 67]. Per the IMB model, we also will investigate differential changes in short-term (in ED) motivation and behavioral skills by information delivery mode, language, and health literacy level. Further, we will (1) assess if increase and retention of knowledge, motivation, and behavioral skills impacts behaviors (HIV testing); (2) examine the interrelationships of model components (e.g., path coefficients [34]); and (3) assess the moderating influence of information delivery mode, health literacy level and language on motivation, behavioral skills and behavior change. Mediation/moderation models using structural equation modeling and other recommended approaches will be used [68–73]. We also will examine other factors potentially associated with HIV re-testing, such as demographic characteristics, study site, and changes in HIV risk-taking behavior over time.

**Table 5 Tab5:** Analyses of secondary and exploratory aims

***Secondary aims***	***Measurements***	***Analytic methods***
**Motivation** (1) attitudes toward need for HIV testing for oneself, (2) beliefs regarding the value of HIV testing, and (3) self-perceived risk for having an HIV infection	HIV testing motivation and behavioral skills questionnaire; post- vs. pre-information delivery	• Paired t-tests or signed rank tests • Generalized linear mixed-effects regression
**Behavioral skills** (1) initiating or seeking of HIV testing, (2) interpretation and response to HIV test results, and (3) assessment of HIV risk and need for repeat testing	HIV testing motivation and behavioral skills questionnaire; post- vs. pre-information delivery	• Paired t-tests or signed rank tests • Generalized linear mixed-effects regression
**Behaviors** (1) testing uptake one-year post-enrollment when offered in the study, (2) testing utilization during the study period, and (3) change in testing utilization one-year pre- vs. post-enrollment	(1) Repeat rapid HIV testing acceptance questionnaire (2) HIV test utilization questionnaire (3) HIV testing history	• McNemar’s tests • Cochran-Mantel-Haenszel’s test • Generalized linear mixed-effects model
***Exploratory aims***	***Measurements***	***Analytic methods***
Utility of brief health literacy instruments	NVS and 3 single-item screens of health literacy level vs. SAHL-S&E and HIV/AIDS and HIV testing knowledge questionnaire	• Pearson/Spearman correlation • Cohen’s Kappa for agreement tests • ROC analyses • Test performance parameters
Information delivery mode preferences and satisfaction	HIV/AIDS and HIV testing information delivery mode preferences and satisfaction questionnaire; post- vs. pre-information delivery	• Paired t-tests or signed rank tests • Generalized linear mixed-effects regression
HIV risk-taking behaviors	HIV risk-taking questionnaire	• McNemar’s tests • Cochran-Mantel-Haenszel’s test • Generalized linear mixed-effects model

For the exploratory aims, we will investigate whether the three brief health literacy screening questions are useful in the ED to identify patients with lower health and lower HIV/AIDS and HIV testing knowledge. Their utility and accuracy to screen for patients with lower health literacy as a substitute for the SAHL-S&E (which is a research instrument not practical for typical ED use), compared to this “gold standard” instrument will be assessed. Also, their ability to identify patients with lower HIV/AIDS and HIV testing knowledge will be assessed using ROC-type analysis, and quantified by test performance parameters (e.g. C-statistic). We also will compare participant satisfaction with the information delivery mode they received and the potential influence of information delivery mode (and differences by language and health literacy level) on changes in HIV risk-taking behavior over the study period and pre- vs. post-enrollment.

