### Study instruments (see Additional file 1 for English-language copies)

Table 2 depicts the study instruments that will be used in the study.

**Table 2 Tab2:** Study instruments description and administration

Instrument	Description	Administration
Screening, eligibility and enrollment questionnaire	• Karliner, et al. Spanish language proficiency & preference [54]	• Baseline
	• Ballard and Tighe Idea Proficiency Test II	• Administered by RA
	• Demographic characteristics & nativity	• < 5 min
	• US acculturation (for Latinos) per the SASH [63]	
	• HIV testing history & HIV-related exclusion screen	
	• Willingness to undergo rapid HIV testing	
	• Adapted from our prior research [19, 21, 45–51]	
Short Assessment of Health Literacy-Spanish & English (SAHL-S&E [22])	• Measures health literacy level	• Baseline
	• Score of ≤14 indicates lower health literacy	• Administered by RA
	• *SAHL-S* is highly correlated with *TOFHLA* (*r* = 0.62), & *SAHL-E* is highly correlated with *REALM* (*r* = 0.94) & *TOFHLA* (*r* = 0.68)	• 3–5 min
	• *SAHL-S&E* reliability is 0.80 & 0.89, respectively	
3 single-item screening tests for health literacy [40–43]	• Derived from the S-TOHFLA	• Baseline
	• AUCs for 3 questions vs. S-TOHFLA (0.66–0.74) vs. REALM (0.72–0.84)	• Administered by RA
		• < 1 min for each question
HIV testing motivation and behavioral skills questionnaire (Behavioral Skills and motivation)	• Measures **Motivation:** (1) attitudes toward need for HIV testing for oneself, (2) beliefs regarding the value of HIV testing, and (3) self-perceived risk for having an HIV infection; and **Behavioral skills:** skills and self-efficacy on (1) initiation/seeking of HIV testing, (2) interpretation and response to HIV test results, and (3) assessment of HIV risk and need for repeat testing	• Baseline (pre- and post-information by video or pictorial brochure)
	• Adapted from our prior research [47, 49, 51] and other author recommendations [74]	• Self-administered by telephone
		• < 2 min
HIV/AIDS and HIV testing information delivery mode preferences and satisfaction questionnaire	• Measures preferences and satisfaction with pictorial brochure or video	• Baseline (pre- and post-information by video or pictorial brochure)
	• Adapted from our prior research [20]	• Self-administered by telephone
	• 1 Pre- and post-information question on preferences with delivery mode	• 1 min
	• 1 post-information question on satisfaction with delivery mode information	

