#### Sample size considerations

The study sample size is *n* = 1200, with equal size strata (*n* = 150) by language, health literacy level, and information delivery mode (Fig. 4). This sample size is based on a 2x2x2 full factorial design and will satisfy the requirements for analysis of the two primary aims and the four alternative hypotheses paired with each aim. The minimum sample size is calculated for a power of 0.80 and a two-sided *α = 0.05* level of significance (Table 3). In general, a larger sample size is needed for greater variation of scores within study arms and strata, lower within-person correlations of scores, and higher loss-to-follow-up. To maximize power, we chose conservative values based upon our prior studies. We increased the sample size by 20% to account for the heterogeneity in patients among the four study sites, and by a conservative additional 25% to account for possible attrition. Based upon other 12-month ED intervention follow-up studies [10], HIV/STD testing studies [57–59], and studies conducted at our own ED [60, 61], a 25% attrition rate at 12 months likely is a worst-case scenario. We expect that our experience and enhanced measures to encourage and facilitate follow-up will result in higher follow-up rates. As of publication of this manuscript, 1165 participants enrolled completed the three-month follow-up.

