### Study analysis (begins at end of recruitment month 43)

#### Enrollment summary and comparison of participants at baseline

We will report on participant enrollment and summarize the reasons for accepting or declining enrollment or drop-out from the study using the Consolidated Standards of Reporting Trials (CONSORT) approach [62]. We will summarize the demographic characteristics, HIV testing history, and health literacy level (measured by the SAHL-S&E [22] and brief instruments) using conventional statistics, such as means/standard deviations, medians/ranges, or counts/frequencies with corresponding 95% confidence intervals (CIs), as appropriate. For Latino participants, we will summarize nativity and US acculturation (measured by the SASH [63, 64]) in a similar manner. We will summarize these baseline characteristics for all participants and as stratified by informational delivery mode (pictorial brochure or video), language preference (English or Spanish), and health literacy level (lower or higher). Next, we will compare the baseline characteristics of study participants between the study arms using Pearson’s Χ^2^ or Fisher’s exact test for categorical variables and Student’s t-test for normally distributed or Wilcoxon’s rank-sum test for non-normally distributed continuous variables to assess the success of the randomization procedure. Any chance imbalances between the two arms will be documented and investigated, and will be adjusted for by including the imbalanced covariate as an independent variable in our subsequent regression analyses, or through a weighted analysis using a propensity score (propensity to be enrolled in the study with weights equal to the inverse of the propensity score) [65]. A two-tailed, *α = 0.05* significance level will be used for all analyses.

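### For 12-month testing uptake and testing during the study, prior HIV testing should be a fixed covariate in the delivery-mode comparison, not one added only if the arms look imbalanced

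*Protocol article*

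**What the plan says.** All references are to the protocol article.

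- **Collection.** Table 2 lists "HIV testing history & HIV-related exclusion screen" in the screening questionnaire, so the variable exists for everyone screened.
- **Knowledge outcomes.** *Secondary analyses of primary aims* will assess the impact of "demographic characteristics, HIV testing history, and testing site for all participants".
- **Re-testing outcomes.** *Secondary aims and exploratory aim analyses* states "Our main secondary aim is assessing HIV re-testing behavior". It then says that other factors possibly associated with re-testing will be examined, "such as demographic characteristics, study site, and changes in HIV risk-taking behavior over time". Testing history is not named there.
- **Table 5.** The behaviours are (1) uptake of the test offered at 12 months, (2) testing during the study and (3) the change in testing from the year before to the year after enrollment. Testing history is the third listed measurement and serves (3). The methods are McNemar's test, the Cochran-Mantel-Haenszel test and a generalized linear mixed-effects model.
- **General adjustment rule.** *Enrollment summary and comparison of participants at baseline* compares baseline characteristics between arms by significance test. Covariates found imbalanced are then handled by regression or propensity weighting.
- **Model form.** *Primary aims analysis* gives the mixed model a covariate term that is not itemised, and allows a logit or probit link for binary outcomes.

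**The concern.** Past testing is a natural predictor of later testing. For outcome (2) it is essentially the baseline value of the outcome; for outcome (1), acceptance of an offered test, it is a related behaviour. Yet the protocol names it for the knowledge outcomes, although its Background reports that knowledge was unrelated to prior testing in the group's earlier Spanish-language trial.

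A rule triggered by imbalance is a weak way to bring in such a covariate, for two reasons.

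- The precision gained by adjusting does not depend on imbalance. If imbalance is judged at the plan's 0.05 level, a fair randomisation flags a given covariate about one time in 20, and the gain is forgone the rest of the time.
- The balance tests compare the two arms, whereas the power statement for re-testing is made by group within strata. An imbalance inside one language-by-literacy stratum can go unseen.

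At stake is some precision on the main secondary aim, at a level where power may already be short.

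**Working it through.** **Inputs from the protocol.** Target: "adequate power to detect a ≥ 15% absolute difference". Conditions: "assumes ≥75% follow-up, β = 0.2, α = 0.05". A two-tailed 0.05 "significance level will be used for all analyses". Cells of 150 "by language, health literacy level, and information delivery mode", so 150 × 0.75 = 112.5 analysed per arm within a stratum.

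**Assumed, because the documents give no figure.** The re-testing rate, the share of prior testers (40%), and the odds ratio linking prior testing to re-testing (3 or 5).

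**Step 1: the plan's own power.** For rates p1 and p2 with mean p̄ and n per arm, power = Φ{[0.15√n − 1.96√(2p̄(1−p̄))] / √(p1(1−p1) + p2(1−p2))}. The stated 0.80 cannot be confirmed without a base rate. At 112.5 per arm it is reached only if the lower rate is at most about 12.5% or at least about 72.5%. For 50% vs 65%: (0.15 × 10.607 − 1.96 × 0.6991) / 0.6910 = 0.319, so power is 0.625.

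**Step 2: from odds ratio to correlation.** With an average rate of 57.5%, let a be the rate in those never tested and b the rate in prior testers, so that 0.6a + 0.4b = 0.575.

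- Odds ratio 3: a = 0.4725, b = 0.729, difference d = 0.256.
- Odds ratio 5: a = 0.431, b = 0.791, d = 0.360.

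Then r = d × √(0.4 × 0.6) / √(0.575 × 0.425) = d × 0.4899 / 0.4943, which gives 0.254 and 0.357.

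**Step 3: gain from always adjusting.** Effective n = n / (1 − r²).

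- Odds ratio 3: 112.5 / (1 − 0.0645) = 120.3; power 0.625 → 0.654, about 3 points.
- Odds ratio 5: 112.5 / (1 − 0.1274) = 128.9; power 0.625 → 0.685, about 6 points.

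Logistic simulations under the same assumptions gave 2 to 3 points at an odds ratio of 3 and 5 to 7 at 5. One set of 1,500 runs per scenario gave 0.64 → 0.66 and 0.61 → 0.66, with a Monte Carlo standard error near 0.012 on each estimate.

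**Step 4: other base rates and correlations (power).**

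| Rates, n per arm | r=0 | 0.1 | 0.2 | 0.3 | 0.4 | 0.5 |
|---|---|---|---|---|---|---|
| 10% vs 25%, 112.5 | 0.846 | 0.850 | 0.861 | 0.878 | 0.903 | 0.932 |
| 30% vs 45%, 112.5 | 0.644 | 0.648 | 0.662 | 0.685 | 0.720 | 0.768 |
| 42.5% vs 57.5%, 112.5 | 0.615 | 0.620 | 0.633 | 0.657 | 0.692 | 0.741 |
| 30% vs 45%, 225 (one factor pooled) | 0.910 | 0.913 | 0.921 | 0.934 | 0.950 | 0.968 |

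A linear-probability simulation at 112 per arm (3,000 runs) agrees in direction and rough size: 0.646 → 0.741 at r about 0.41 (30% vs 45%) and 0.631 → 0.699 at r about 0.4 (42.5% vs 57.5%).

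**Step 5: chance imbalance within a stratum.** The between-arm difference in the share of prior testers has standard deviation √(2 × 0.4 × 0.6 / 112) = 0.065, so a 95% range of ±12.8 points. An imbalance at the edge of that range shifts the unadjusted mode difference by 12.8 × 0.256 = 3.3 points (odds ratio 3) or 12.8 × 0.360 = 4.6 points (odds ratio 5), against a target of 15.

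**The case against.** The strongest reply is that this is silence in a condensed article rather than a stated choice. Much of it stands.

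- A reader might infer that the re-testing comparisons are unadjusted. The text does not say so. The list of factors is open and describes an association analysis, not the covariate set of the mode comparison, and the un-itemised covariate term of the mixed model does not exclude prior testing. A full covariate list may sit in a full protocol or SAP that is not shown.
- A reader might infer that chance imbalance goes uncorrected. The baseline-comparison section contradicts that between arms; what remains is that the correction is conditional and is not described within strata.
- A reader might infer that change in risk-taking, measured after randomisation, enters the mode-effect model. The protocol names it only as a factor to examine for association.
- The contrast with knowledge is modest: testing history is named there in sub-group analyses, while the main knowledge comparison mentions only demographic characteristics as an example.
- Outcome (3) uses prior testing directly, so the point does not reach it.
- Everyone in the longitudinal phase has just accepted an ED test, so the strength of past testing as a predictor in this group is unknown.

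What survives is narrower. The one route that the article does state is triggered by imbalance, and two of the three listed methods are simple tests that need not include the covariate.

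**Conclusion.** The point holds as an improvement to outcomes (1) and (2), not as an error. The protocol does not commit to prior HIV testing as a covariate in these mode comparisons, and its stated rule would add it only on imbalance. With 40% prior testers, 112 per arm and 50% vs 65%, always including it is worth about 2 to 3 power points at an odds ratio of 3 and about 5 to 7 at 5. At r of 0.2 or below the gain is 0 to 2 points. All of this rests on an assumed base rate and association.

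It would be wrong to infer that the missing covariate explains a power shortfall or that adding it cures one. In the mid-range rows of the table, power stays at 0.74 to 0.77 even at r = 0.5. The unstated base rate behind the within-stratum power claim matters more.

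**What to change.** For outcomes (1) and (2), state before analysis that the mode comparison uses the logistic form of the planned generalized linear model, with mode, language, literacy level and baseline HIV testing history always included, whether or not an imbalance is seen. For comparisons within a stratum, language and literacy are constant, so the model reduces to mode and testing history. Fix the coding of testing history in advance, for example tested in the past 12 months, tested earlier, or never; outcome (3) already requires the pre-enrollment year. A standardised risk difference alongside the odds ratio would keep the result on the scale of the 15-point target, but that is a reporting choice.

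The cost is one sentence of analysis wording. The variable is already collected, and sample size and conduct do not change.

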We employed the Spanish-language video and questionnaire in a randomized, controlled, non-inferiority trial at an ambulatory medical clinic, an ED, and a community-based organization in Providence evaluating the efficacy of the video vs. comparable orally-delivered information from an HIV test counselor (a RA) in regards to short-term HIV/AIDS and HIV testing knowledge [21]. We enrolled 18–64-year-old primarily Spanish-speakers (*n* = 150) in the trial. Randomization was stratified by health literacy level (lower vs. higher) as measured by the Short Assessment of Health Literacy-Spanish and English (SAHL-S&E), which has strong psychometric properties in assessing health literacy [22]. After the video or orally-delivered information, HIV/AIDS and HIV testing knowledge applicable to CDC recommendations was assessed through audio-computer self-interviews (ACASI) using our previously developed 25-item questionnaire. Of the 150 participants, 39% met criteria for lower health literacy. For all participants, the mean scores for correct items on the questionnaire for the video (20.4; 95% CI: 19.5~ 21.3) and orally-delivered information (20.6; 95% CI: 19.7~ 21.5) groups (Δ = − 0.15; 95% CI: -1.4~ 1.1) were similar, satisfying the a priori non-inferiority criterion. Of those who watched the video, 93% stated that they were well or very well informed, and of those who received information orally, 96% stated that they were well or very well informed. Mean knowledge scores among lower health literacy participants were similar (18.3 [video] vs. 19.6 [in-person]; *p* < 0.30). In multivariable linear regression analyses, lower mean knowledge scores were related only to health literacy level (β − 2.4; 95% CI: -3.8, − 1.1), and not demographic characteristics (age, gender, race, insurance status, years of formal education, nativity, US acculturation), study arm (video or in-person information), study location (ambulatory medicine clinic, ED, or community-based organization) or prior HIV testing.

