Although it is reasonable to assume that delivery of HIV/AIDS and HIV testing knowledge should be tailored to meet the needs of the estimated 15–40% of ED patients with lower health literacy [24–27], there is no published research on this topic. In particular, we do not know if pictorial brochures and videos are equivalently efficacious modes of delivering HIV/AIDS and HIV testing information, or if one mode is better than the other and should be preferred. Also unknown is how delivery mode affects retention of HIV/AIDS and HIV testing knowledge over time. Prior research indicates that intensive interventions [28–32] lead to retained HIV/AIDS and HIV testing knowledge. However, there have been no studies evaluating retention of knowledge from less intensive—yet much more likely to be used—modes of information delivery (e.g., brochures, videos*)*. Because previously studied intensive interventions (e.g., multiple skill-building sessions, peer counseling) are impractical in the ED setting, shorter, easier-to-deliver, yet efficacious modes are needed. In addition, it is important for maintain the operational efficiency of EDs to know if, when, how, and for whom information needs to be provided for HIV re-testing.

Information is believed to be necessary but not sufficient as a stand-alone component of HIV-related behavior change [33]. Although the videos we created address HIV- and HIV testing-related motivation and behavioral skills commensurate with the Information-Motivation-Behavioral Skills (IMB) model [34, 35], their impact on HIV test seeking behavior, utilization/acceptance of repeat HIV testing, and engaging in HIV risk-taking behaviors remains unknown. Furthermore, no studies have examined HIV re-testing after ED-based testing, and few non-ED studies have investigated factors associated with acceptance of HIV re-testing [36–39]. Understanding reported reasons for accepting or declining HIV re-testing is important for guiding future HIV re-testing interventions and approaches as well as addressing testing barriers. If HIV/AIDS and HIV testing information, and more specifically how it is delivered (pictorial brochure vs. video, according to health literacy level and language), impacts HIV re-testing behaviors, there would be better justification for providing this information and more attention on how (and to whom) it should be delivered.

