#### Exploratory aims

To help apply the findings from our trial to ED practice, we will (1) explore brief, easy-to-use, single-question methods [40–43] that ED non-research staff could use to identify lower health literacy patients who would benefit more from information delivered via video or a pictorial brochure. We will also (2) assess participant satisfaction with their assigned information delivery mode and (3) their self-reported changes in HIV risk-taking behavior over the one-year follow-up period.

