**Fig. 2 Fig2:**
[figure not shown]
Participant recruitment feasibility estimates by study site, language, and health literacy level

**Table 1 Tab1:** Descriptions of study sites

Location	Annual ED patient volume	ED patient demography	HIV prevalence
UAB Hospital ED	55,000 visits	• 54% black, 42% white, 3% Latino	• 0.4% in Jefferson County
Birmingham, AL	18–64-year-olds/year	• 53% female, 47% male	• 0.3% seroprevalence among those tested in ED
UCMC ED	83,000 visits	• 51% black, 44% white, 1% Latino	• 0.15% in Cincinnati metro area
Cincinnati, OH	18–64-year-olds/year	• 48% female, 42% male	• 0.4% seroprevalence among those tested in ED
Olive View-UCLA	63,000	• 5% black, 20% white, 70% Latino	• 0.38% in Los Angeles
Medical Center ED	18–64-year-olds/year	• 51% female, 49% male	• 4.4% seroprevalence among those tested in ED
Los Angeles, CA		• 75% of Latinos primarily speak Spanish	
Rhode Island Hospital ED	87,000 visits	• 10% black, 60% white, 30% Latino	• 0.2% in Providence metro area
Providence, RI	18–64-year-olds/year	• 48% female, 52% male	• 0.01% seroprevalence among those tested in ED
		• 50% of Latinos primarily speak Spanish	

We will recruit a total of 1200 patients (600 English-speakers and 600 Spanish-speakers) over a two-year period. The RA at each ED will recruit 300 ED patients over four shifts/week for 48 weeks/year for 2 years (384 shifts total/RA), and devote one shift/week to participant follow-up, training, and administrative duties. To reach recruitment goals, each RA must recruit at least 0.78 patients/shift. In comparison, we recruited 1.25 Spanish-speakers/shift in our previous R21 study (R21NR011997). Our recruitment estimates are conservative and assume that 25% of ED patients are study ineligible (see study inclusion criteria), 50% would decline participation, and only 25% would be classified as lower health literacy. As shown in Fig. 2, ample participants are available for recruitment at each ED per these assumptions.

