**Fig. 3 Fig3:**
[figure not shown]
Trial protocol flow diagram

For those who agree to be screened (verbal consent will be obtained), the RAs will administer the screening, eligibility and enrollment questionnaire (*See* Additional file 1). The screening questionnaire consists of questions about demographic characteristics and HIV testing history. Patients who self-identify as HIV infected or are enrolled in conflicting HIV studies (e.g., HIV vaccine, HIV pre-exposure prophylaxis [PrEP], or a study that measures HIV testing over time or similar outcomes as this study) will not be eligible and will be thanked for their time. Next, the RA will administer the three health literacy questions [40–43]. The RA then will administer the SAHL-S&E [22] to stratify participants by health literacy level (lower or higher). During the course of the latter portion of the study if a participant’s health literacy level exceeds the quota for the study site, he/she also will not be eligible for participation.

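### The brief health-literacy questions are not assessed against benefit by delivery mode, the stated exploratory aim, and their agreement statistics from a sample fixed at 50% lower literacy would not carry over to an ED

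*Protocol article*

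**What the plan says.** **The aim.** Under Exploratory aims, the article wants brief questions that ED staff could use to "identify lower health literacy patients who would benefit more from information delivered via video or a pictorial brochure".

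**The analysis.** Table 5 gives the comparison as "NVS and 3 single-item screens of health literacy level vs. SAHL-S&E and HIV/AIDS and HIV testing knowledge questionnaire". The methods listed are Pearson/Spearman correlation, Cohen's kappa, ROC analyses and test performance parameters. The text below the table treats the three questions as a possible substitute for the SAHL-S&E and as a marker of low HIV knowledge. It gives the C-statistic as its example of a performance parameter.

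**The sample.** Sample size considerations sets 1200 participants "with equal size strata (*n* = 150) by language, health literacy level, and information delivery mode". Under Enrollment, late in recruitment a patient whose literacy level "exceeds the quota for the study site, he/she also will not be eligible for participation". The three questions and then the SAHL-S&E are given before that exclusion is applied.

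**Expected literacy in EDs.** The Background refers to the "estimated 15–40% of ED patients with lower health literacy". Study sites and recruitment feasibility assumes that "only 25% would be classified as lower health literacy". In the group's earlier Spanish-language trial, "39% met criteria for lower health literacy".

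**The concern.** There are two gaps between what the aim asks and what the analysis delivers.

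First, a question that classifies literacy, or picks out people who know little about HIV, does not by that fact show who learns more from a video than from a brochure. No section relates the brief questions to the difference between modes. The Primary aims analysis tests mode by SAHL-S&E class, and the covariates named under Secondary analyses of primary aims do not include the brief questions. An ED could be offered a question for choosing the mode without any estimate of how the mode effect differs by its answer.

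Second, kappa and correlation depend on the share of lower-literacy patients in the sample, as would any predictive values. In enrolled participants that share is set by design and lies above the whole range cited for EDs. The article mentions neither reweighting nor which patients, screened or enrolled, enter this analysis.

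**Working it through.** **1. The enrolled literacy mix.** 2 languages × 2 literacy levels × 2 modes = 8 cells, and 8 × 150 = 1200, which reproduces the stated total. Lower literacy fills 4 × 150 = 600, and 600/1200 = 50%.

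**2. Effect of the mix on the measures.** The article gives no accuracy of the questions against the SAHL-S&E. Table 2 gives earlier AUCs of 0.66–0.74 against the S-TOFHLA and 0.72–0.84 against the REALM. I assume that these carry over, and take the point Se = Sp on an equal-variance binormal ROC curve: Se = Sp = Φ(z(AUC)/√2). For AUC 0.74 this is Φ(0.643/1.414) = 0.675.

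With prevalence p and share screening positive q = p·Se + (1−p)(1−Sp):
- PPV = p·Se/q
- NPV = (1−p)·Sp/(1−q)
- kappa = (po − pe)/(1 − pe), with po = p·Se + (1−p)·Sp and pe = p·q + (1−p)(1−q)

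Example, AUC 0.74 and p = 0.25 (unrounded Se = Sp = 0.6754):
- q = 0.1689 + 0.2434 = 0.4123
- PPV = 0.1689/0.4123 = 0.410
- NPV = 0.5066/0.5877 = 0.862
- pe = 0.1031 + 0.4408 = 0.5439, so kappa = (0.6754 − 0.5439)/0.4561 = 0.288

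| AUC (Se = Sp) | Prevalence | Kappa | PPV | NPV |
|---|---|---|---|---|
| 0.66 (0.615) | 50% | 0.229 | 0.615 | 0.615 |
| | 40% | 0.222 | 0.515 | 0.705 |
| | 25% | 0.183 | 0.347 | 0.827 |
| | 15% | 0.132 | 0.220 | 0.900 |
| 0.74 (0.675) | 50% | 0.351 | 0.675 | 0.675 |
| | 40% | 0.342 | 0.581 | 0.757 |
| | 25% | 0.288 | 0.410 | 0.862 |
| | 15% | 0.216 | 0.269 | 0.922 |
| 0.84 (0.759) | 50% | 0.518 | 0.759 | 0.759 |
| | 40% | 0.508 | 0.677 | 0.825 |
| | 25% | 0.446 | 0.512 | 0.904 |
| | 15% | 0.354 | 0.357 | 0.947 |

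The correlation between the two binary classes (phi) at AUC 0.74 falls from 0.351 at 50% to 0.309 at 25%.

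**3. Direction.** With unequal Se and Sp, kappa at 50% and then 25% prevalence is:
- Se 0.40, Sp 0.95: 0.350 and 0.412 (rises)
- Se 0.60, Sp 0.85: 0.450 and 0.443 (nearly flat)
- Se 0.85, Sp 0.60: 0.450 and 0.333 (falls)

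**4. What does not change.** Selection is by SAHL-S&E class, so Se, Sp and AUC against that class are the same at any mix. In a simulation of the C-statistic against low knowledge (assumed Se = Sp = 0.70, literacy deficit 2.4 points, SD 3, fixed knowledge cut-off) the values were 0.562 at 50%, 0.553 at 25% and 0.539 at 15%, a small shift.

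**5. How much of a mode-by-literacy difference a screen passes on.** Suppose a screen carries no information about benefit beyond SAHL-S&E class (an assumption). The difference in mode effect between screen-positive and screen-negative patients is then the SAHL-S&E difference times (PPV + NPV − 1). At AUC 0.74 and 25% prevalence the factor is 0.410 + 0.862 − 1 = 0.272. Table 3 adds 0.75 points for a two-way interaction (2.25 − 1.5), so 0.75 × 0.272 = 0.20 points on a 25-item scale. In the 50% sample the factor is 0.351, giving 0.26 points.

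**6. Precision of that interaction.** With the Table 3 values SD 3 and correlation 0.7, the SD of the change score is √(2 × 9 × 0.3) = 2.32. With about 300 per mode-by-screen cell, the standard error is 2.32 × √(4/300) = 0.27. An effect of 0.26 points is then about one standard error, so the result must be read from its interval.

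**The case against.** The best defence is that the plan works in two steps. The primary model tests whether the mode effect differs by SAHL-S&E literacy, and the exploratory analysis asks whether a short question can stand in for the SAHL-S&E. If both answers are yes, tailoring by the question has support. Identifying lower-literacy patients is also part of the aim and is answered directly. This stands, so the planned analysis is not irrelevant, although a reader might infer that. It does not make the link direct: step 5 shows that most of a literacy difference can be lost when an imperfect screen replaces the SAHL-S&E.

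A reader might also infer that all the accuracy results will be inflated. The article does not support that. ROC analysis is listed and the C-statistic is the only parameter given as an example, and against the SAHL-S&E it does not depend on the mix. PPV and NPV are never named. NPV would be understated in the enrolled sample, and kappa can rise, fall or stay flat. At 40% prevalence the symmetric-case kappa hardly moves (0.351 to 0.342). Nor is it general that most positive screens would be wrong at 25%: that share is 59% at AUC 0.74 but 49% at AUC 0.84. The 25% itself is presented as a conservative recruitment assumption.

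Finally, nothing restricts the analysis to enrolled participants, and an article may leave the analysis set to a fuller document. That is fair, and so the point on prevalence is conditional on enrolled participants being used.

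**Conclusion.** The point holds as an inexpensive improvement to an exploratory aim. The aim is worded as benefit from a delivery mode, while the analysis stops at literacy class and knowledge level, leaving only an indirect link through the primary interaction. If the screening statistics come from enrolled participants, kappa, correlation and any PPV or NPV describe a 50% mix that lies outside the cited 15–40%. In the symmetric case, going to 25% lowers kappa by 0.05 to 0.07 (0.229 to 0.183 at AUC 0.66, 0.518 to 0.446 at AUC 0.84), lowers PPV by 25 to 27 points and raises NPV by 14 to 21 points.

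These sizes rest on AUCs measured against other reference tests and on an assumed symmetric cut-off. The direction for kappa is not general.

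The NVS appears in Table 5 but not in Table 2 or the enrolment steps, and the text under Table 5 speaks only of the three questions. This is a clerical mismatch that does not affect the analysis of those questions. The conclusions on the primary and secondary aims are unaffected.

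**What to change.** 1. In the Aim 1 and Aim 2 models, replace SAHL-S&E class with each brief question in turn and report the mode-by-screen interaction on knowledge improvement and retention, with its confidence interval, labelled exploratory. Given step 6, a non-significant result should not be read as absence of a difference.
2. Make sensitivity, specificity and AUC against the SAHL-S&E the main accuracy measures. Give kappa, correlation and any PPV or NPV from all patients who completed the three questions and the SAHL-S&E at screening, including those excluded by the quota, or reweight enrolled participants to that literacy mix. Report by language, and state the analysis set.
3. Reconcile the NVS entry in Table 5 with Table 2: remove it, or list the instrument if it is administered.

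The cost is analysis wording. The three questions and the SAHL-S&E are already given before the quota exclusion, but it should be confirmed that the answers of patients turned away are kept. The downsides are a separate flow count for screened patients and possibly less favourable predictive values.
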